# Direct warming and rehydration method in frozen embryo transfer: study protocol for a pragmatic, multi-center, double-blinded, two-arm randomized controlled trial

**DOI:** 10.1186/s13063-026-09663-x

**Published:** 2026-05-18

**Keywords:** Cryopreservation, Embryo warming, Vitrification, Direct warming, Live birth rate, Cost-effectiveness

## Abstract

**Background:**

Embryo cryopreservation through vitrification is widely used to store surplus embryos for future transfer. Traditional multi-step warming methods are both time-consuming and costly. This study evaluates the clinical outcomes and the effectiveness of a novel direct warming method for frozen embryo transfer (FET) in comparison to the conventional multi-step method.

**Methods:**

This is a pragmatic, two-arm, double-blinded randomized controlled trial (RCT) comparing the new direct warming method with the conventional multi-step method. Participants undergoing FET will be randomly assigned to either the direct warming method or the conventional warming protocol. The primary outcomes are the clinical pregnancy rate (CPR), ongoing pregnancy rate (OPR), the live birth rate (LBR), miscarriage rate, and cost-effectiveness. Secondary outcomes include identifying clinical differences among various brands of warming media, embryo storage devices, and embryo culture media through subgroup analyses. A sample size of 578 participants is planned, allowing for a 5% loss to follow-up.

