### Objectives {7}

#### Primary objective

The primary objective is to evaluate the clinical outcomes and cost-effectiveness of the novel direct warming method compared to the conventional multi-step warming method for FET in terms of clinical pregnancy rate (CPR), ongoing pregnancy rate (OPR), live birth rate (LBR), miscarriage rate, and time efficiency, cost-effectiveness.

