### Outcomes {12}

#### Primary outcomes

The primary outcome of this study is to evaluate the clinical efficacy of the new direct warming method for FET compared to the conventional multi-step warming method. The key measures for the primary outcome include:Clinical pregnancy rate: defined as the presence of at least one intrauterine gestational sac detected via ultrasound at 6–8 weeks of gestation. Multiple pregnancies (two or more gestational sacs) are counted as one clinical pregnancy.Ongoing pregnancy rate: defined as the proportion of pregnancies that progress beyond 6–8 weeks, with at least one viable fetus with a heartbeat confirmed via ultrasound.Live birth rate: the proportion of participants who achieve a live birth, defined as the delivery of a live baby after 24 weeks of gestation.Miscarriage rate: the proportion of pregnancies resulting in pregnancy loss after the confirmation of clinical pregnancy.Cost-effectiveness: an evaluation of the cost savings achieved by using the new method, including reductions in time, materials, and labor compared to the conventional method.The equation for consumable cost: (total consumable cost of conventional warming in all centers/total cycle number of the conventional warming in all centers)/(total consumable cost of direct warming in all centers/total cycle number of the direct warming in all centers) × 100%.The equation for time cost: (total minutes spent on conventional warming in all centers/total cycle number of the conventional warming in all centers)/(total minutes spent on direct warming in all centers/total cycle number of the direct warming in all centers) × 100%.The equation for labor cost: (total hours spent on conventional warming in all centers/total cycle number of the conventional warming in all centers * role-specific hourly rates)/(total hours spent on direct warming in all centers/total cycle number of the direct warming in all centers * role-specific hourly rates) × 100%.

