### Sample size {14}

The sample size calculation was based on preliminary data indicating approximately a 5% increase in the live birth rate with the new method compared to conventional warming. With type I error (*α*) set at 0.05 and type II error (*β*) set at 0.2 (80% power), and assuming a clinically significant difference of 20% in the worldwide clinical pregnancy rate, the required sample size per arm is 275, calculated using MedCalc 15.6.1. To account for a 5% loss to follow-up, a total of 578 participants will be enrolled (289 per arm). Given that the total number of participating centers is currently undetermined, the leading center, IVFHK-CUHK, will serve as the core recruitment site. This center can independently recruit at least 578 participants.

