## Assignment of interventions: blinding

### Who will be blinded {17a}

This trial will be conducted as a double-blinded study. Both the trial participants and the clinical team will be blinded to the group assignments after the allocation to interventions has been completed. Neither group will have access to information about whether participants are in the intervention group (direct warming method) or the control group (conventional warming method).

Outcome assessors will also be blinded to the group assignments to ensure unbiased evaluation of primary and secondary outcomes, including embryo survival rates, pregnancy rates, and live birth rates. Data analysts will be blinded to the group allocation during the analysis phase to prevent bias in data interpretation.

The use of sequentially numbered, opaque, sealed envelopes ensures allocation concealment until the point of intervention, maintaining blinding throughout the trial.

Embryologists cannot be blinded in this trial.

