## Statistical methods

### Statistical methods for primary and secondary outcomes {20a}

All analyses will follow an intention-to-treat (ITT) approach, with statistical significance set at *p* < 0.05 and 95% confidence intervals (CI). Primary outcomes, including embryo survival rate, pregnancy rate, clinical pregnancy rate, and live birth rate, will be analyzed using logistic regression models, adjusting for potential confounders such as cause of infertility, previous ART cycle, and embryo quality. Chi-square tests or Fisher’s exact tests will be used for categorical outcomes like embryo survival, and logistic regression will report odds ratios (OR) for pregnancy and live birth rates.

Secondary outcomes, including implantation rate and multiple gestation pregnancy rate, will be analyzed using generalized linear models (GLM) and chi-square tests. Thawing time will be compared using *t*-tests or Mann-Whitney *U* tests for non-normal data. Cost-effectiveness will be evaluated through cost-effectiveness analysis (CEA), while post-thaw embryo quality will be assessed using standard grading criteria and analyzed with chi-square tests. Missing data will be handled using multiple imputation to maintain the integrity of the results. An extra sensitivity analysis will be conducted if loss to follow-up is more than 5%.

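### Several unranked primary outcomes, listed differently from section to section, leave the deciding outcome open; if any one of the four clinical outcomes counts as success, the false-positive rate is about 12 to 13%, not 5%.

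*Protocol article*

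**What the plan says.** The protocol article describes its primary outcomes in several places, and they do not agree.

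- **Abstract, Methods:** "The primary outcomes are the clinical pregnancy rate (CPR), ongoing pregnancy rate (OPR), the live birth rate (LBR), miscarriage rate, and cost-effectiveness".
- **Outcomes {12}:** the same five, introduced by "The key measures for the primary outcome include", with no order among them.
- **Primary objective {7}:** "clinical pregnancy rate (CPR), ongoing pregnancy rate (OPR), live birth rate (LBR), miscarriage rate, and time efficiency, cost-effectiveness", which makes six items.
- **Statistical methods {20a}:** "Primary outcomes, including embryo survival rate, pregnancy rate, clinical pregnancy rate, and live birth rate, will be analyzed using logistic regression models". Embryo survival and pregnancy rate are not in the Outcomes list.
- **Discussion:** miscarriage, pregnancy and live birth rates are called primary.

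On error control, the statistical methods section says: "All analyses will follow an intention-to-treat (ITT) approach, with statistical significance set at *p* < 0.05 and 95% confidence intervals (CI". The sample size section {14} says: "With type I error (*α*) set at 0.05 and type II error (*β*) set at 0.2 (80% power". It starts from "preliminary data indicating approximately a 5% increase in the live birth rate with the new method compared to conventional warming", then assumes a 20% difference in clinical pregnancy rate, and arrives at 275 per arm. The document states no order of testing, no split of the significance level, and no rule on whether one or all of the primary outcomes must be significant.

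**The concern.** A 5% error rate describes one decision. Here the reader cannot tell which result makes that decision. The sample size section would normally settle it, but it names two outcomes. A gain in clinical pregnancy with no difference in live birth, or a difference in miscarriage alone, could each be reported as a positive primary result under this text, and so could embryo survival under the statistical methods section. The trial is declared a superiority trial, so a claim made that way would carry a higher false-positive rate than the design states. Two analysts following the article faithfully could also reach opposite headline conclusions from the same data.

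**Working it through.** **1. The lists side by side**

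| Item | Abstract and {12} | Objective {7} | Statistics {20a} |
|---|---|---|---|
| Clinical pregnancy (CPR) | primary | primary | primary |
| Live birth (LBR) | primary | primary | primary |
| Ongoing pregnancy (OPR) | primary | primary | not named |
| Miscarriage | primary | primary | not named |
| Cost-effectiveness | primary | primary | not named as primary |
| Time efficiency | not a separate item | primary | not named as primary |
| Embryo survival | not listed | not listed | primary |
| Pregnancy rate | not listed | not listed | primary |

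Only CPR and LBR are primary everywhere. The firm contradiction is in the last two rows.

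**2. Does the sample size identify the deciding outcome?**

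The control rate is not given, nor whether 5% and 20% are absolute or relative, so 275 cannot be derived from the stated inputs alone. Two-sided 0.05, 80% power, 1:1, with m the mean of p1 and p2:

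n = [1.96·√(2m(1−m)) + 0.8416·√(p1(1−p1) + p2(1−p2))]² / (p1−p2)²

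- CPR, 20% relative, assumed 57.5% vs 69%: m = 0.6325; (1.3364 + 0.5697)² / 0.115² = 3.633 / 0.013225 = 274.7, so 275. This matches the plan's figure, but the control rate was chosen to do so.
- CPR, 20 points absolute: at most 97 per arm at any control rate. This does not match.
- LBR, 5 points absolute, control 30 to 50%: 1,377 to 1,565 per arm. This does not match.

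The number 275 is therefore compatible with CPR under one reading and not with an absolute 5-point gain in LBR, while the text cites both.

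**3. False-positive rate if any one clinical outcome counts**

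Cost-effectiveness is left out because no hypothesis test is named for it. The other four are not independent: ongoing pregnancies are a subset of clinical pregnancies, and live births a subset of ongoing ones. I simulated 400,000 trials per scenario with no treatment effect, 275 per arm, and unadjusted two-sided z-tests at 0.05. CPR, OPR and LBR were counted per participant and miscarriage per clinical pregnancy. All rates are assumptions: CPR 40, 50 or 60%; OPR/CPR with LBR/OPR of 90% with 95%, 85% with 93%, or 80% with 90%.

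- Lowest (40%, 90%, 95%): 11.9%.
- Middle (50%, 85%, 93%): 12.8%.
- Highest (60%, 80%, 90%): 13.1%.
- CPR, OPR and LBR only, over the same grid: about 8 to 10%.
- All four required to be significant: about 0.1%.

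The Outcomes section words OPR as a proportion of pregnancies; counting it that way gives about 14%. The unstated success rule thus moves the error rate from far below 5% to more than double it, while the assumed rates hardly matter.

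**4. Power if live birth is the deciding outcome**

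Power = Φ{[|p1−p2|·√n − 1.96·√(2m(1−m))] / √(p1(1−p1) + p2(1−p2))}

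For 40% vs 45% and n = 275: (0.8292 − 1.3703) / 0.6982 = −0.775, so power is 21.9%. Over control rates of 30 to 50% it runs from 23.9% down to 21.6%.

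**The case against.** The strongest reply is that multiplicity rules commonly sit in a statistical analysis plan, which is not shown, and that a general 0.05 threshold does not exclude a hierarchy. This stands as far as the missing adjustment goes. It does not rescue the outcome lists: which outcome is primary is for the protocol to fix, and this one fixes it in conflicting ways.

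A second reply is that the list in the statistical methods section is open, since it begins with a word meaning that more may follow. This also stands in part. That section cannot be said to have dropped OPR or miscarriage, and although it discusses cost-effectiveness in the same paragraph as the secondary outcomes, it does not label it secondary. An open list still does not explain why embryo survival and pregnancy rate are primary there and absent from the Outcomes section.

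A reader might also infer more than the documents support:

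- That five tests give 1 − 0.95⁵ = 22.6%. This assumes five independent tests. Three of the outcomes are nested, and cost-effectiveness has ratios and a cost-effectiveness analysis but no named test.
- That the interim look raises the rate further by a known amount. The interim section states no significance level for efficacy, so no figure can be attached.
- That embryo survival is scored by unblinded staff, because "Embryologists cannot be blinded in this trial". The same section says that outcome assessors are blinded, embryo survival included, and no section says who scores it.

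**Conclusion.** The point holds in this form: the article names several unranked primary outcomes, adds others in the objective and the statistics section, and ties one sample size to two outcomes, so the deciding outcome is open. If success on any one of CPR, OPR, LBR or miscarriage counts, the chance of at least one false positive is about 12 to 13% rather than 5%. That size rests on assumed event rates, 275 per arm, unadjusted tests in place of the planned adjusted logistic regression, and an any-one rule that the text permits but does not state. Under an all-must-succeed rule there would be no inflation. The inconsistency between the lists rests on no assumption and should be corrected before any outcome is compared by arm, including at the interim analysis.

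**What to change.** Name one primary outcome, counted per randomised participant. Two candidates follow from the document. Live birth fits the aim stated in the introduction and is the outcome of the preliminary data. CPR is the outcome for which the sample size section states the difference. Make all other outcomes secondary, either tested in a fixed order or reported with confidence intervals only. Use the same list in the abstract, {7}, {12}, {14}, {20a} and the Discussion.

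Then restate the power in {14} for the chosen outcome, giving the control rate and whether the difference is absolute or relative. If CPR is chosen, an assumed 57.5% vs 69% would keep 275 per arm. If live birth is chosen and the 5% gain is absolute, the article should say that 275 per arm gives about 22 to 24% power at assumed control rates of 30 to 50%, or N must change.

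The cost is an amendment of wording plus a recalculation. The other outcomes lose primary status, and the stated power may look less favourable. Keeping four clinical outcomes as any-one-wins primaries would cost more: at 0.05/4 = 0.0125 each, power on one outcome falls from 80% to about 62% in the 57.5% vs 69% scenario, and restoring 80% needs 391 per arm before loss to follow-up.

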**Discussion:**

Preliminary studies have shown that the direct warming method offers comparable or slightly higher live birth rates than conventional methods. Moreover, it significantly reduces thawing time and associated costs, offering a faster, cost-effective option for FET. This trial has the potential to improve accessibility to ART by reducing procedural costs and increasing efficiency without compromising clinical outcomes.

**Trial registration:**

ClinicalTrials.gov NCT06741748. Registered on 19 November 2024.

## Introduction

### Background and rationale {6a}

Infertility affects approximately one in six individuals globally, making assisted reproductive technologies (ARTs) essential for many couples attempting to achieve pregnancy [1]. Among ART procedures, frozen embryo transfer (FET) has become the most frequently performed technique, surpassing 2 million cycles annually since the first live birth achieved via frozen embryo transfer using slow freezing [2, 3]. Vitrification has since emerged as the dominant method for embryo cryopreservation, significantly improving survival rates compared to the earlier slow-freezing method [4]. Although vitrification has replaced slow freezing, the corresponding advancements in embryo warming techniques have not progressed as rapidly.

The process of thawing vitrified embryos requires precise and rapid warming rates, specific thawing solutions, and the expertise of skilled embryologists to ensure optimal survival rates [5]. Conventionally, the multi-step warming process gradually dilutes and removes cytotoxic cryoprotectants, maintaining extracellular osmolality to avoid osmotic shock. However, this method typically requires 15–20 min and incurs significant costs, approximately 5500 HKD per procedure. Not only is this multi-step approach costly, but it also extends the time required to prepare embryos for transfer.

Our research introduces a novel direct warming method that offers a faster, cost-effective alternative. Unlike other ultra-fast warming methods, which utilize sucrose or trehalose in thawing solutions, our approach employs embryo culture mediums without any cryoprotectants [6–8]. This method has demonstrated a 100% survival rate in over 100 donated human blastocysts. The entire warming process is completed in just 1 min, reducing the time required by 90% and lowering costs by 80% [9].

This innovative method challenges conventional perceptions of embryo warming. While vitrification has revolutionized cryopreservation, leading to improved safety and clinical outcomes for frozen embryo transfers, the embryo warming process has lagged in comparison [10]. Current laboratory protocols rely on commercial thawing kits that involve multiple steps and specific cryoprotectants [11]. Among these, ultra-fast warming methods using cryoprotectants like sucrose or trehalose are commonly employed to manage osmotic shock during embryo warming [5–7]. While these methods are effective, they involve multiple steps and carry the risk of residual toxicity from the cryoprotectants. In contrast, our direct warming method eliminates the need for cryoprotectants, providing a simpler approach that controls the risk of osmotic stress, avoids cryoprotectant-related toxicity, and reduces potential handling errors. This method not only speeds up the warming process and lowers material costs but also improves consistency and reproducibility, making it a more efficient and reliable alternative in clinical practice.

The aim of this study is to show the direct warming method is at least equivalent to the conventional method plus can save billions of dollars from patients with the same healthy take-home baby rate.

### Objectives {7}

#### Primary objective

The primary objective is to evaluate the clinical outcomes and cost-effectiveness of the novel direct warming method compared to the conventional multi-step warming method for FET in terms of clinical pregnancy rate (CPR), ongoing pregnancy rate (OPR), live birth rate (LBR), miscarriage rate, and time efficiency, cost-effectiveness.

#### Secondary objective

The secondary objective is to evaluate the impact of technical variations (warming media, storage devices, and culture media) on clinical outcomes between the direct warming method and the conventional multi-step method.

### Trial design {8}

This is a two-arm, double-blinded, parallel-group, multi-center, randomized controlled trial (RCT) with a superiority framework. The trial will compare the efficacy and safety of the new direct warming method against the conventional multi-step warming method for FET.

Participants will be randomized in a 1:1 allocation ratio into one of two groups:Intervention (arm 1): the new direct warming method.Control (arm 2): standard care using the conventional multi-step warming method.

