## Interventions

### Explanation for the choice of comparators {6b}

In this trial, the comparator chosen is the conventional multi-step warming method, which is the current standard of care for thawing vitrified embryos in ART procedures [12]. This method has been widely used in clinical practice due to its established safety and effectiveness, making it an appropriate comparator for evaluating the new direct warming method.

The conventional multi-step method involves a series of steps that gradually remove cryoprotectants and rehydrate the embryo, ensuring its post-thaw survival. It typically requires 15–20 min to complete and is performed by trained embryologists. Despite its widespread use, the multi-step process is time-consuming and can incur significant costs, making it a useful benchmark for comparison with the new direct warming method, which aims to simplify the procedure and reduce both time and cost while maintaining or improving clinical outcomes.

The choice of this comparator allows the study to directly assess whether the new direct warming method can offer a more efficient and cost-effective alternative without compromising the success rates of embryo survival, implantation, pregnancy, and live birth.

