### Methods in analysis to handle protocol non-adherence and any statistical methods to handle missing data {20c}

The primary analysis will be conducted on an ITT basis, which includes all participants as randomized, regardless of protocol adherence or deviations. Participants who discontinue the intervention will still be analyzed in the group to which they were originally assigned to preserve the randomization process.

To address potential missing data, multiple imputation techniques will be employed. Missing values will be imputed based on available baseline and follow-up data, ensuring that the analysis maintains sufficient statistical power. Sensitivity analyses will also be performed to assess the robustness of the results, comparing complete case analyses to those using imputed data.

Per-protocol analyses may also be conducted as a secondary analysis to assess the outcomes among participants who fully adhered to the study protocol.

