## Discussion

This trial protocol presents the design of an RCT comparing the novel direct warming method to the conventional multi-step warming process for FET. The trial seeks to determine whether this simplified method, which eliminates cryoprotectants and shortens the warming process, offers comparable clinical outcomes in terms of embryo survival, pregnancy rates, live birth rates, or any adverse events.

Given that maternal age is a well-established factor affecting fertility outcomes, participants are stratified into defined age groups [17]. This stratification ensures that age-related differences in embryo quality or implantation potential are accounted for in the analysis, enhancing the rigor and validity of the results.

The novel direct warming method offers significant advantages. Unlike other ultra-fast warming methods that use cryoprotectants such as sucrose or trehalose to prevent osmotic stress [7, 8], our method eliminates the need for cryoprotectants altogether. This reduces the complexity of the process, minimizes the risk of cryoprotectant-related toxicity, and significantly reduces the time required for warming, from approximately 20 min to just 3 min. This efficiency could optimize clinical workflows, particularly in high-volume fertility clinics, while reducing costs by eliminating the need for multiple thawing solutions.

Our simplified approach directly challenges the conventional understanding of embryo warming, which emphasizes multi-step processes to gradually remove cryoprotectants [12, 18]. By demonstrating that a single-step approach can achieve comparable embryo survival and pregnancy outcomes, this trial has the potential to shift the current paradigm. While some may argue that the absence of cryoprotectants increases the risk of osmotic stress, our preliminary data suggest that this risk can be effectively managed without compromising embryo viability or pregnancy rates [9, 19]. This novel method also offers practical advantages in terms of standardization and ease of use, which could make it an attractive option for fertility clinics aiming to streamline their protocols.

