However, as a multi-center study, the findings may still be influenced by site-specific variations in clinical practices and patient demographics, which could impact generalizability. While the inclusion of multiple centers enhances the study’s external validity, further large-scale trials in diverse settings will be necessary to confirm broader applicability. Additionally, while miscarriage, pregnancy, and live birth rates are primary outcomes, long-term follow-up on birth outcomes, including potential congenital abnormalities, will be crucial to fully assess the safety of this novel method.

This trial protocol is positioned to provide valuable insights into whether the direct warming method can serve as a more efficient and equally effective alternative to conventional multi-step warming. If successful, it could simplify clinical protocols, reduce operational costs, and challenge the traditional understanding of embryo warming processes in ART.

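### The trial is designed and tested for superiority, but its stated aim is to show at least equivalence; a non-significant result could not support that aim

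*Protocol article*

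**What the plan says.** Trial design {8} describes a "randomized controlled trial (RCT) with a superiority framework". Sample size {14} sets alpha at 0.05 and power at 80%, and arrives at 275 per arm (289 enrolled per arm, 578 in total) from an assumed difference between methods. Statistical methods {20a} specifies intention-to-treat analysis, p < 0.05, 95% confidence intervals, and odds ratios for pregnancy and live birth. No non-inferiority or equivalence margin appears anywhere in the article.

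The purpose is worded differently. Background and rationale {6a}: "The aim of this study is to show the direct warming method is at least equivalent to the conventional method". Explanation for the choice of comparators {6b} asks whether the new method "can offer a more efficient and cost-effective alternative without compromising the success rates". The Discussion asks whether it "offers comparable clinical outcomes in terms of embryo survival, pregnancy rates, live birth rates" and whether it "can serve as a more efficient and equally effective alternative to conventional multi-step warming". The per-protocol analysis is optional in {20c}: "Per-protocol analyses may also be conducted as a secondary analysis".

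**The concern.** The advantage sought is a faster, cheaper procedure, and the clinical question put in three sections is whether outcomes are preserved. A superiority test answers another question. If it is significant in favour of direct warming, it supports the aim. If it is not, it shows only that a difference was not detected, and the article gives no margin by which the confidence interval could be judged.

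At stake is the main conclusion. A non-significant p-value, read beside an aim of showing equivalence, invites the conclusion that the methods are equivalent. Practice could then change on cost grounds while a meaningful loss of live births had not been excluded.

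**Working it through.** **Inputs from the article.** 275 evaluable per arm, 1:1 allocation, alpha 0.05, power 80%, and a preliminary gain of about 5% in live birth rate.

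**Assumptions.** The article gives no control live birth rate; I use 35–50%. It does not say whether the 5% is absolute or relative; I take it as 5 absolute points and label results that depend on this. It does not say whether alpha is one- or two-sided; I take two-sided.

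**The plan's own figure.** 275 does not follow from the stated inputs alone. For control rates of 20–60%, a 5-point gain needs 1094–1565 per arm and a 20-point gain needs 82–97 (two-sided, no continuity correction). A 20% relative gain gives about 275 only at an unstated control rate of 57–58%. The step to 289 does reproduce: 275 × 1.05 = 288.75. Below, 275 is taken as given.

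**Formulas.** Let p be the control live birth rate.
- SE at equal rates = √(2p(1−p)/275); 95% half-width = 1.96 × SE.
- SE at a 5-point gain = √{[p(1−p) + (p+0.05)(0.95−p)]/275}; superiority power ≈ Φ(0.05/SE − 1.96).
- Non-inferiority power at equal rates, margin M = Φ(M/SE − 1.96).
- Margin giving 80% power at equal rates = (1.96 + 0.8416) × SE.

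Example at p = 0.35: SE = √(0.455/275) = 0.0407; half-width = 0.080. At a 5-point gain, SE = √(0.4675/275) = 0.0412 and power = Φ(1.21 − 1.96) = 0.23. For a 10-point margin, Φ(2.46 − 1.96) = 0.69.

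| p | 95% half-width (points) | Superiority power, +5 points | Non-inferiority power, 10-point margin, equal rates | Margin for 80% power, equal rates (points) |
|---|---|---|---|---|
| 0.35 | 8.0 | 23% | 69% | 11.40 |
| 0.40 | 8.2 | 22% | 67% | 11.70 |
| 0.45 | 8.3 | 22% | 65% | 11.89 |
| 0.50 | 8.4 | 22% | 65% | 11.95 |

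With all 289 per arm, the half-width at p = 0.35 is 1.96 × √(0.455/289) = 0.078, and at p = 0.50 it is 1.96 × √(0.5/289) = 0.082, so the picture does not change.

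**Reading.** An observed difference of zero leaves a loss of about 8 points inside the interval. If the true gain is 5 points, roughly 77–78% of such trials would be non-significant on live birth. A relative 5% is a smaller gain (2 points at a 40% control rate), so power would be lower still.

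**The case against.** The operative sections agree with each other: design, sample size and analysis are all about a difference, and the formal primary objective in {7} is neutral. The comparator section also speaks of maintaining or improving outcomes, and the Abstract of comparable or slightly higher live birth rates. On this view the equivalence language is loose background prose. That limits the fault but does not remove it: {6a} states the aim in so many words, and {6b} and the Discussion repeat it.

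Several stronger readings are tempting and are not supported:
- A reader might infer that the trial cannot meet its aim at all. A significant superiority result would meet it; the gap is confined to the non-significant case.
- A reader might infer that no valid conclusion is possible after a non-significant result. {20a} plans 95% confidence intervals, which show what losses are excluded. What is missing is a rule for judging them.
- A reader might infer that equal methods would give a non-significant trial 95% of the time. That holds for one outcome and one look. The article lists several primary outcomes and an interim analysis.
- A reader might take non-significance as the expected result whatever the truth. It is likely if the true effect is near zero or near 5 points. It is not likely for a 20-point gain (power above 99%), or for a 20% relative gain at a control rate near 57–58% (power about 80%).
- A reader might infer that non-inferiority could be adopted with no extra participants. That holds only for a margin of about 11–12 points, or if the new method is truly better.
- A reader might count the optional per-protocol analysis as an error. Under superiority it is ordinary; it matters only if the framework changes.

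**Conclusion.** The contradiction stands and bears on the conclusion the trial may draw; it is not a detail that an analysis plan could supply, because the article itself fixes both the framework and the aim. As written, a non-significant result cannot support the stated aim. It would leave a loss of about 8 live births per 100 participants unexcluded, given 275 per arm and an assumed live birth rate of 35–50%. That a non-significant result is likely (superiority power about 22–23%) rests on the further assumption that the preliminary 5% is an absolute gain and close to the truth.

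**What to change.** Reconcile {6a} with {8}, by one of two routes.

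**Minimum change: keep superiority.** Remove the equivalence wording from the aim in {6a}, and the comparable and equally effective wording from {6b} and the Discussion as intended conclusions. Add: *A non-significant result is not evidence of equivalence and will be reported as the 95% confidence interval for the risk difference.* {20a} at present names odds ratios, so the risk difference has to be added. This costs wording only.

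**Alternative: non-inferiority, if that is the real aim.**
- Name one primary outcome, live birth per randomised participant.
- Have the sponsor fix and justify a margin before enrolment and before any interim look. Fixing it merely before unblinding is too late: embryologists are not blinded {17a}, non-pregnant participants may be told their arm {16b}, and the steering committee, which includes the principal investigator, sees interim data {21b, 5d}.
- Declare non-inferiority if the lower limit of the two-sided 95% interval for the risk difference (direct minus conventional) lies above minus the margin. Test superiority only afterwards, and state how the interim efficacy stop is handled.
- Require both intention-to-treat and per-protocol analyses.
- Restate power. At 275 per arm and equal true rates of 35–50%, a 10-point margin has about 65–69% power and 80% power needs about 11.4–12.0 points. Narrower margins need more participants unless the new method is truly better.

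This route costs a protocol and registry amendment, a public margin that may look wide, and possibly a larger trial. Trial status describes the study as preparing for recruitment; if enrolment has begun, the margin can no longer be set before it, and the first route is the sound one.
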